#### Process measures

The goal of process evaluation in this study is to understand the factors that can influence the success of complex interventions [55]. Guided by the Medical Research Council (MRC) guidance on process evaluation, we developed a framework process evaluation for the HWePS intervention to evaluate the key constructs of context (external factors related to the intervention), implementation process, implementation (fidelity, dose, reach, and adaption), and mechanisms of impact (unintended outcomes and mediating pathways) [56] (Fig. 2). The process evaluation will use a mixed methods design. Quantitative and qualitative data will be collected using standardized questionnaires, case studies, documents, and focus group interviews guided by semi-structured questions, etc.

**Fig. 2 Fig2:**
[figure not shown]
Process evaluation constructs and data collection methods adapted from the UK Medical Research Council (MRC) [56]

### Sample size and recruitment

This HWePS intervention study is part of a larger community-wide health equity initiative, starting with a community-wide health and wellness survey conducted from November 2020 to January 2021. The sample for the community-wide survey consisted of approximately 700 older adults in the intervention area and 500 older adults in the control area, which is approximately 19.2% and 7.6% of all older adults in each area, respectively (as of October 2020). Informed consent concerning the entire study was obtained by the research team prior to initiating the survey.

The recruitment of participants into the HWePS intervention is based on the roster of older adults who participated in the community survey. The sample size of the HWePS intervention is calculated using the G*Power 3.1.9.2 program as follows. We hypothesize an effect size (as the input parameter for G*Power) of 0.2 based on previous community-based health and wellness interventions for older adults’ self-rated health [57–59]. The required number of samples is identified as 265 for each arm, by choosing the MANOVA approach in two repeated measures (90% power, 5% α error) in two independent groups. With an estimated dropout rate of 30% in the intervention period, a total sample size of approximately 379 participants per arm needs to be recruited.

Enrollment into the study will progress sequentially by clusters based on residents’ *tong* (smaller neighborhood). At the beginning of each intervention period, all individuals in the cluster will be contacted by the research team by telephone and given a brief explanation of the program. We will directly visit the homes for recruitment of those older adults who do not respond to the phone calls due to low technology literacy, wariness, or other reasons. Upon agreeing to participate in the study, the participant will be scheduled for a health survey for baseline data collection by an external assessor. Recruitment and baseline data collection will be simultaneously conducted. Eligibility and consent to participate is reconfirmed by phone or in-person during the intervention recruitment.

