## Methods/design

### Study design

The Health and Wellness Program for Seniors (HWePS) is a two-arm, non-randomized, controlled cluster trial that seeks to evaluate a theory-guided, technology-enhanced, integrated health-equity intervention model for older residents in urban, low-income communities in Seoul, Korea, during the COVID-19 pandemic. The HWePS targets complex, multi-level factors influencing disparities, including factors at the individual, interpersonal (social), and community levels [10]. The schedule of enrollment, intervention, and assessment of the intervention is summarized in Fig. 1. A total of two measurements (pre- and post-intervention) are conducted on each individual. A 12-week case management program aiming to build self-care skills and practice with a nurse coach and peer support is rolled out in three clusters and spans an overall study period of approximately 12 months. A community-wide, multi-channel information delivery service aiming to promote heath literacy, and a healthy-living, healthy-aging initiative aiming to build community capacity and resources/networks are continued throughout the entire intervention period. This intervention was developed through a mixed-methods approach guided by 6SQuID [31]; various stakeholders have been involved in developing the heath disparity intervention project, starting with its inception and continuing throughout the entire intervention development process, which will be published as a separate paper. The trial described here is prospectively registered at ISRCTN. This protocol has been reported following TREND guidelines [32].

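### On the stated inputs, 265 is the total sample size over both arms, not the number per arm, so the per-arm figure and the 90% power do not belong together

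*Protocol article*

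**What the plan says.** The relevant text is in the protocol article under Sample size and recruitment, with the number of measurements given under Study design.

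- Effect size: "We hypothesize an effect size (as the input parameter for G*Power) of 0.2". The source given is earlier community interventions that measured self-rated health in older adults.
- Result and method: "The required number of samples is identified as 265 for each arm, by choosing the MANOVA approach in two repeated measures".
- Error rates and groups: "90% power, 5% α error) in two independent groups".
- After an assumed 30% dropout: "a total sample size of approximately 379 participants per arm needs to be recruited".
- Measurements: "A total of two measurements (pre- and post-intervention) are conducted on each individual".

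The paragraph gives no standard deviation, pre-post correlation or design effect. It does not name the MANOVA module used (between, within or interaction).

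**The concern.** The paragraph gives both the inputs and the result, so the result can be checked. In this family of power calculations the sample size that enters the noncentrality is the total over all groups. A total that is read as a per-arm number doubles the sample and separates the stated power from the stated effect.

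What is at stake is how the trial will be interpreted. Readers will use the 90% figure to judge what a null result on self-rated health rules out. If n, effect size and power do not fit together, the paragraph does not tell them which effect the trial detects with 90% power. The same figure also sets the recruitment target of 379 per arm.

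**Working it through.** **Inputs** (all from Sample size and recruitment, except the number of measurements, which is from Study design): f = 0.2, 2 groups of equal size, 2 measurements, alpha 0.05, power 0.90, dropout 30%.

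**Formula.** With two groups and two measurements, the MANOVA group-by-time test is an F test with 1 and N − 2 degrees of freedom and noncentrality λ = N·f², where N is the total over both groups. No pre-post correlation enters this form.

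**Reproducing 265.** With f² = 0.04:

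| Total N | λ = 0.04·N | Power |
|---|---|---|
| 264 | 10.56 | 0.8993 |
| 265 | 10.60 | 0.9004 |
| 530 (265 per arm) | 21.20 | 0.9958 |

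The smallest N that reaches 90% is 265, as a total. Split over two arms, 265/2 = 132.5, so about 133 per arm.

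**Dropout step.** 265/0.7 = 378.6, which rounds up to 379. The division is right, but it carries the total forward as a per-arm number. From 133 per arm it gives 133/0.7 = 190 per arm.

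**Does any other MANOVA option with input 0.2 give 530 in total?** The total N required is:

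| Variant (f = 0.2) | Total N |
|---|---|
| Between-groups, correlation 0 / 0.5 / 0.8 / 1 | 134 / 199 / 239 / 265 |
| Within or interaction with f scaled by the correlation, 0 / 0.5 | 134 / 68 |
| Global effects, two responses | 320 |
| Interaction, 95% power | 327 |
| Interaction, alpha 0.025 | 313 |

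None comes near 530.

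**What 265 per arm detects with 90% power.** Solving for f at N = 530 gives f of about 0.14 (0.1415 on the search grid). For two equal groups d = 2f, so d is about 0.28 in standard deviations of the change score.

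**Which unstated inputs would give about 265 per arm?**

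- A raw standardised difference of 0.2 with a pre-post correlation of 0.75, analysed as change. The difference in units of the SD of change is 0.2/√(2 × 0.25) = 0.283, so f = 0.141 and λ = 530 × 0.02 = 10.6. Power at 265 per arm is 0.901, and the solved requirement is 263 per arm.
- The same raw difference with baseline adjustment and a correlation of 0.7: 268 per arm.
- f = 0.1 with zero correlation: 528 in total. This contradicts the stated 0.2.
- f = 0.2 with a design effect of 2: 530/2 = 265 effective participants, power 0.900.

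**The case against.** **The cause is inferred.** The article does not name the module, so nobody outside the team can be certain that a total was misread. This stands, and the most that can be said is that the match to the unit makes it very likely. That the stated inputs do not give 265 per arm does not depend on the cause.

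**The slip is conservative.** It enlarges the sample and changes neither the analysis nor the type I error rate. On the article's own individual-level formula, a null result would be more informative about f = 0.2 than claimed. This stands too, and it limits the point to a correction of the stated figures.

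**A reader might infer that the trial is underpowered**, by taking 0.2 as a standardised difference between arms. The article does not support this. It calls 0.2 the G\*Power input parameter and says the MANOVA approach was chosen, which points to f and not to a difference in standard deviations. Nor can one say that the power is wrong however 0.2 is read, since a raw difference of 0.2 with a correlation near 0.75 gives about 90% at 265 per arm. The fair statement is that the inputs given do not reproduce the figure.

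**99.6% could mislead.** The trial compares one intervention with one control neighbourhood and enrols by smaller neighbourhood units, while 99.6% holds only for independent individuals. As an illustration, a design effect of 2 brings 265 per arm back to 0.900 and a design effect of 3 gives 0.753. The article states no design effect. The caution is right, so the figure should not appear without that qualification.

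**Conclusion.** The point holds as an inconsistency between the stated inputs and the stated result. For f = 0.2 with two groups, two measurements, 90% power and 5% alpha, the required sample is 265 in total: about 133 per arm before dropout and about 190 per arm after it. The article states twice that, 265 and 379 per arm. With 265 completers per arm, power for f = 0.2 is about 99.6%, and the effect detected with 90% power is f of about 0.14.

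These figures assume that 0.2 is the f-type input of the MANOVA procedure, as the text indicates, that the arms are equal in size, and that individuals are independent. They do not show that 379 per arm is too many or too few, because whether it suffices once clustering is allowed for is a separate question.

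**What to change.** Keep the recruitment target and correct the paragraph in one of two ways.

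1. If 0.2 is f: state that 265 is the total required for f = 0.2. Then state that 265 completers per arm give 90% power for f of about 0.14 (about 0.28 SDs of change). Add that these figures assume independent individuals and make no allowance for clustering.
2. If 265 per arm was intended: state the input that yields it, namely the metric of the 0.2, the assumed pre-post correlation or the design effect.

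The cost is the rewording of one paragraph, with no added participants and no change in procedures. Under Trial status the article reports that data collection is ongoing and analysis has not begun, so on that status the correction can be made before results are known.

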### Study setting and participants

The HWePS is being conducted in two urban neighborhoods (*dong*; 1 intervention *dong*, 1 control *dong*) within Jungnang-gu in Seoul, Korea. Jungnang-gu, one of the easternmost districts of Seoul, is home to a higher-than-average proportion of older adults living alone (8.7% vs. 7.1% in Seoul) and people receiving national basic livelihood security (7.0% vs. 4.1% in Seoul). Out of the 25 districts in Seoul, Jungnang-gu has the third lowest fiscal independence rate as of 2020 [33]. The intervention and control areas (*dong*) within Jungnang-gu have similar proportions of older residents, but they are geographically remote from each other in order to prevent any spillover effect. The selection of these particular neighborhoods was also based on health statistics about the areas as well as input from the public health center in Jungnang-gu regarding service needs in the intervention areas.

Study participants include older adults residing in the intervention and control areas who consent to participate in the research study. Participants come from a pool of individuals who participated in a community-wide community health and wellness survey conducted in late 2020 [34]. Inclusion criteria for participants are as follows: 1) aged 65 or older, 2) non-frail based on the K-FRAIL [35], 3) not a long-term care insurance beneficiary, and 4) not planning to move away from the area during the intervention period. Study participation is entirely voluntary, and participants may withdraw from the study at any time.

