### Assignment of interventions and blinding

Participant assignment into the intervention group or the control group is solely based on area of residence. Participants reside in 15 *tongs* in the intervention area and 15 *tongs* in the control area, and are divided into 3 clusters matched based on mean age and residential type (apartment vs. house).

Considering the nature of the study, limited single-blinding is applied to the intervention, as participants will not be told whether they reside in the intervention or control area, but researchers will be aware of the allocation. Upon giving informed consent, participants in the intervention group will receive an explanation of the entire HWePS intervention, while control group participants will receive an explanation of only the health information component. Assignments will not be explicitly expressed to external assessors but may be inferred throughout the course of the study. An independent data analyst blinded to the assignments will receive a cleaned dataset without any identifiable information.

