### Data analysis plan

#### Effect evaluation

Descriptive statistics will be used to analyze data concerning the participants’ demographic and baseline characteristics. Baseline differences between the intervention and control group will be analyzed using an independent sample t-test or the Mann–Whitney U-test for continuous data and the Chi-square test for categorical data. The primary analysis is an evaluation of the interventional effect of the HWePS program in the intervention area as compared to the control area. We will apply mixed effects models and generalized estimating equations adjusting for sample characteristics. In case there are significant baseline differences between groups, propensity score matching methods will be used. Subgroup analyses will be performed for sociodemographic factors (e.g., age, sex, income, etc.) and health status (e.g., frailty), and two paired t-tests will be applied for those variables collected only in the intervention group. All statistical analyses will be carried out using SAS 9.4 (Cary, NC, USA) and p-values with α ≤ 0.05 will be considered significant.

Effect analysis will be conducted based on the intention-to-treat (ITT) principle, in which all participants who participated in the HWePS study will be included regardless of intervention dose or protocol adherence. Imputation methods will be implemented to handle missing data to enable ITT analysis. Sensitivity analyses will be conducted to assess the effects of inclusion in various groups within the samples.

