We designed the HWePS to develop and rigorously test the effectiveness of an intervention that simultaneously engages older people and neighbors (as CLHLs) and enlists community-level resources and strengths to promote the health and wellness of older people in a low-income urban community during COVID-19. If effective, the intervention, as a preventive, integrated community care model, may add great value to current efforts to reduce health disparities among urban, lower-income older populations with double (age- and income-related) risks for inequality. First, instead of a professional-driven model, the intervention is an older person-led, community-engaged, professional-support model. As a theory-driven, evidence-based public health model, the HWePS will address health inequality by empowering older adults to recognize that they are responsible for their own health, understand their own health status and risks using a decision-support tool, develop with a nurse coach their own plan for self-care skill-building, and practice it daily with peer support enhanced by ICT tools. Second, the intervention educates and empowers participating CHNs for the “visiting community service center service” program in Seoul [16], and designs and demonstrates new roles for the CHNs, whose current roles are mainly as direct care providers. In the HWePS program, these nurses act as leaders of a multidisciplinary care team, coaches for empowering older people, and mobilizers of community resources and strengths, helping to increase community capacity to build healthy living conditions in collaboration with various stakeholders in the community as well as the multidisciplinary care team. The required preparation, resources, and also challenges for the transformation of CHNs’ roles can be identified and shared with various stakeholders, including CHNs themselves and also administrators and policymakers at various levels involved in this intervention project and more broadly.

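### An area-assigned trial with one dong per arm is sized as independent individuals, so its 5% error and stated power hold only if the two dongs would otherwise have changed alike

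*Protocol article*

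**What the plan says.** The Study design section states that the programme "is a two-arm, non-randomized, controlled cluster trial". Study setting and participants adds that "The HWePS is being conducted in two urban neighborhoods", one for each arm. Under Assignment of interventions and blinding, "Participant assignment into the intervention group or the control group is solely based on area of residence", and "Participants reside in 15 *tongs* in the intervention area and 15 *tongs* in the control area"; these tongs are grouped into three matched roll-out clusters.

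Sample size and recruitment uses G*Power with an effect size of 0.2 and reaches 265 per arm "by choosing the MANOVA approach in two repeated measures (90% power, 5% α error) in two independent groups". A 30% dropout allowance raises this to 379 per arm. No ICC or design effect appears.

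For the analysis, Effect evaluation says: "We will apply mixed effects models and generalized estimating equations adjusting for sample characteristics". Propensity score matching follows if baseline differences are significant. The level at which the models carry clustering is not named. The Discussion describes the aim as follows: "We designed the HWePS to develop and rigorously test the effectiveness of an intervention".

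**The concern.** The sizing contradicts the declared design. People in the same tong share services, peers and surroundings, and everyone in an arm shares one dong. The calculation treats all of them as independent.

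The more serious layer is the dong. With one per arm, a programme effect and any other reason for residents of the two dongs to change differently are the same contrast. The article itself makes such reasons plausible: the areas were chosen partly on health statistics and on local input about service need, they lie far apart, and the study runs while the pandemic is closing or cutting services. The challenges listed in the Discussion do not include this limit. Ethics and dissemination makes roll-out to the rest of the district and the city depend on the programme being effective. The meaning of a significant primary result, and a policy decision built on it, are therefore at stake.

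**Working it through.** **1. The plan's own figures**

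Inputs from Sample size and recruitment: effect size 0.2, power 90%, alpha 5%, two groups, two measurements, dropout 30%.

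- Dropout step: 265 / (1 − 0.30) = 378.6, so 379. This reproduces. It also accounts for the whole step from 265 to 379, so no design effect was applied after the 265.
- The 265: the article names neither the effect-size metric nor the test within the MANOVA family. Take f(V) = 0.2 and the within-between interaction, with noncentrality λ = N·f² and df (1, N − 2). At N = 265, λ = 265 × 0.04 = 10.6 and power is 0.9004. So 265 comes out exactly, but as the **total** N.
- On the same inputs, 265 per arm means N = 530, λ = 21.2 and power 99.6%.
- Other readings do not give 265 per arm from the stated inputs. The MANOVA between-factors test gives totals of 134 to 239 for pre/post correlations of 0 to 0.8. A standardized difference of 0.2 gives 526 per arm. With that difference, a change score at correlation 0.75 (263 per arm) or ANCOVA at 0.7 (268 per arm) comes close, but the article states no correlation.

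**2. Dong level, one per arm**

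Let ρ be the share of the variance in individual change that lies between dongs. The documents give no value, so a range is assumed.

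- Variance inflation: 1 + (n − 1)ρ
- True error of a nominal two-sided 5% test: 2·[1 − Φ(1.96/√inflation)]

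| Assumed dong ICC | Inflation, n = 265 | True error, n = 265 | Inflation, n = 379 | True error, n = 379 |
|---|---|---|---|---|
| 0.001 | 1.26 | 8% | 1.38 | 10% |
| 0.002 | 1.53 | 11% | 1.76 | 14% |
| 0.005 | 2.32 | 20% | 2.89 | 25% |
| 0.01 | 3.64 | 30% | 4.78 | 37% |

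More participants make the error worse, because the nominal standard error shrinks while the dong component does not. A tong random effect does not help either: a dong effect shifts all 15 tongs of an arm together, so it leaves no trace in the variation among tongs within that arm.

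**3. Tong level, 15 per arm**

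Mean size is 265/15 = 17.67 and the design effect is 1 + 16.67·ICC, again over an assumed range. What this does to power depends on which reading of 265 is right. Normal approximation throughout.

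| Assumed tong ICC | Design effect | Power if 265 is G*Power's total and 265 per arm are analysed | Power if 265 per arm is truly the 90% size |
|---|---|---|---|
| 0 | 1.00 | 99.6% | 90% |
| 0.01 | 1.17 | 98.9% | 85% |
| 0.02 | 1.33 | 97.9% | 80% |
| 0.05 | 1.83 | 92.5% | 67% |

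On the first reading, power reaches 90% when the design effect is 21.2/(1.96 + 1.2816)² = 2.02, that is, an ICC of (2.02 − 1)/16.67 = 0.06. With a t test on 28 df, power at ICC 0.05 is 90.7%, so the limit is nearer 0.05.

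**The case against.** The strongest defence has four parts.

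- **Power.** A reader might infer that tong clustering pulls power below 90%. The documents do not show this. On the only reading that reproduces 265 from the stated inputs, 265 per arm is about twice the independent-data requirement and absorbs a tong ICC up to about 0.05. A shortfall needs a different metric or an unstated correlation. This defence stands, although it means that the stated 90% and the per-arm 265 do not agree on that reading either.
- **Level differences.** A reader might infer that every difference between the neighbourhoods is counted as effect. Each person is measured before and after, so a contrast of change removes stable differences. The dongs also share a district and have comparable shares of older people, and the roll-out clusters are matched on average age and housing type. This stands, and it narrows the problem to differential change.
- **Analysis.** A reader might infer that tong is ignored in the models or that standard errors go uncorrected for few clusters. The article says neither. Mixed models and GEE can both carry a tong level, and such detail may sit in an analysis plan that is not shown. This stands.
- **Size and openness.** The error rates rest on assumed ICCs, and the two-area, non-randomized design is openly declared. The magnitudes are indeed illustrative. The direction is not: any positive between-dong variance in change takes the error above 5%. Declaring the design also does not make the unconditional power and error statement correct.

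**Conclusion.** The point holds in conditional form. The sample-size paragraph treats an area-assigned trial as two samples of independent individuals. With one dong per arm, the 5% error and any power figure hold only if the between-dong variance in change is zero. No analysis plan can remove that condition, because the design leaves no degrees of freedom for estimating the variance; a plan can only disclose it. Under assumed dong ICCs of 0.001 to 0.01, the true error at 265 per arm runs from about 8% to 30%.

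A loss of power from tong correlation is not established. It ranges from immaterial to substantial (67% at an assumed ICC of 0.05), depending on whether 265 was a total or a per-arm number, and the article leaves this unclear.

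A significant result would show that these two neighbourhoods changed differently. Attributing the difference to the programme requires the further assumption that they would otherwise have changed alike.

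**What to change.** 1. **Sample size.** Restate the paragraph with a tong-level design effect for 15 tongs per arm over a stated ICC range. Name the G*Power test and effect-size metric, and reconcile the 265 per arm with the program's total N.
2. **Primary model.** Include tong as a clustering level in the mixed model or GEE, with a correction suited to about 30 clusters. If the analysis plan already does this, a cross-reference is enough.
3. **Dong-level sensitivity.** Pre-specify a table that inflates the standard error for dong ICCs of 0.001 to 0.01. At 265 per arm, the multipliers on an individual-level standard error are √1.26 = 1.12, √1.53 = 1.24, √2.32 = 1.52 and √3.64 = 1.91. State beside it that error and power are conditional on no between-dong variance in change.
4. **Conclusion.** Word it as a comparison of change between two neighbourhoods, and bring the Discussion's statement of aim into line.

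The cost is protocol and analysis-plan wording plus one table. The precision statement becomes less favourable and the conclusion weaker. No new data are needed, and Trial status reports that analysis had not begun, so the changes can be fixed beforehand.
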